**Methods:**

One hundred ten upper and lower limb amputees suffering from RLP will be recruited and assigned randomly to one of the surgical interventions (TMR, RPNI, or neuroma transposition) in an equal allocation ratio. Complete evaluations will be performed during a baseline period prior to the surgical intervention, and follow-ups will be conducted in short term (1, 3, 6, and 12 months post-surgery) and in long term (2 and 4 years post-surgery). After the 12-month follow-up, the study will be unblinded for the evaluator and the participants. If the participant is unsatisfied with the outcome of the treatment at that time, further treatment including one of the other procedures will be discussed in consultation with the clinical investigator at that site.

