### Assignment of intervention

#### Sample size

Sample size calculation is based on previous studies investigating the surgical treatments for neuroma pain [12, 13] and based on the limited number of available participants. To receive a minimum power of 80% from a Fisher’s non-parametric permutation test assuming a standard deviation of TMR and RPNI to be 2.2 and 3.3 for control [12] with a mean difference of 2.0 and at 5% significant level between the randomised groups in an allocation ratio of 2:1 (TMR and RPNI vs control), it is estimated that at least 84 (*n* = 28 per group) participants are required. With the same assumptions, but instead looking at one reconstruction technique compared to control in a ratio of 1:1 (TMR vs control, RPNI vs control), 99 participants (*n* = 33 per group) are needed to reach minimum power of 80% with a Fisher’s non-parametric permutation test with a mean difference of 2 NRS and at 5% significant level. The drop-out rate is expected to be around 10%; therefore, a total of 110 participants will be aimed to be randomised.

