### Statistical analyses

The statistical analyses will be performed pairwise comparing the techniques in the following scheme:Reconstruction techniques compared to control: TMR and RPNI vs control (2:1)Individual comparison of each reconstruction technique compared to the control: TMR vs control (1:1) and RPNI vs control (1:1)Comparison between the reconstructive techniques: TMR vs RPNI (1:1)

Statistical analysis for the primary outcome, the mean difference of change in NRS score (0–10) of residual limb pain between baseline and 1-year follow-up between the two reconstructive surgical methods and control (2:1), will be performed with an ANCOVA for comparison of independent means on ITT population at 5% significance level, adjusted for the stratification (minimisation) variables NRS pain at baseline, level of amputation, and site. Imputation will be performed with the last observation carried forward (LOCF). A sensitivity analysis will be performed using a two-sided non-parametric permutation test for comparison of independent means on the ITT population. A complementary analysis will be performed for the primary variable of the PP population. The main results will be the mean difference with 95% CI, effect size, and *p*-value.

Secondary analyses will be performed unadjusted, between the two groups on both ITT and PP-population with Fisher’s non-parametric permutation tests for continuous variables, with the Mantel–Haenszel chi-square test for ordered categorical variables, and with Fisher’s exact test for dichotomous variables and performed adjusted with ANCOVA for continuous variables and with multivariable logistic regression for dichotomous variables.

Exploratory analyses will be performed to investigate the differences in groups such as lower vs upper extremity, right vs left extremity, female vs male, reason for amputation, baseline NRS (medium 4–6, high 7–10), time since amputation, and age. These exploratory analyses will be done within each group and then pooled together. All significance tests will be two-sided and conducted at the 5% significance level. When half of the study population has passed the 1-year follow-up, an independent committee including a medical expert and a statistician will examine the data with regard to safety.

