## Discussion

Investigation in pain-related studies is challenging due to an absence of objective evaluation methods. Pain is a subjective experience that is difficult to quantify independently among participants. In our study design, we have tried to mitigate this problem by using different protocols and questionnaires for pain tracking that have previously been used in clinical settings.

One of the main challenges in this RCT is to recruit a sufficient number of potential candidates meeting our inclusion criteria within an acceptable time. For example, it took over 3 years for Dumanian et al. (2019) to gather 28 participants who met their study criteria [12], and this study was performed in the USA (with a larger amputee population compared to Sweden, Italy, Canada, Chile, and the UK). According to Sweden’s amputation and prothesis registry for lower extremities (SwedeAmp) yearly report in 2019, the mean age of amputation for women is 78 and for men is 72 years old. Furthermore, 61% of all amputated women and 58% of all amputated men are in the range of 70–89 years old, and 84% of all Swedish amputees have either diabetes and/or vascular disease. We expect this to add a significant challenge in the volume of participants required. Our recruitment approach therefore includes close contact with prosthetic centres, orthopaedics, and hand surgeons in the participating hospitals.

The surgical treatment approach requires that the participants undergo surgery; thus, general surgical risk applies, including but not limited to those associated with anaesthesia, the possibility of superficial or deep bacterial infections, and delayed wound healing. Even though the surgical approaches have shown potential for postamputation pain reduction [12, 13], there is a risk that the treatment results in no relief or a worse pain situation for the participant. This may lead to a need for increased pain suppression medication.

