## Trial status

This clinical study was registered at ClinicalTrials.gov on 17 August 2021 with registration number NCT05009394. This is protocol version 4 (2022–12-21). Recruitment of participants is expected to take place in early 2023 and is expected to be completed in 2025.

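### The only independent safety review the article describes waits until half the participants have passed 1 year, by when about 83–100% would be randomised under uniform recruitment

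*Protocol article*

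**What the plan says.** The Statistical analyses section gives the committee one sentence. Its timing is: "When half of the study population has passed the 1-year follow-up, an independent committee", with medical and statistical members. Its task is stated as: it "will examine the data with regard to safety".

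The recruitment period is in Trial status: "Recruitment of participants is expected to take place in early 2023 and is expected to be completed in 2025". The size is in Sample size: "The drop-out rate is expected to be around 10%; therefore, a total of 110 participants will be aimed to be randomised". The follow-up clock runs from surgery; in the abstract, "follow-ups will be conducted in short term (1, 3, 6, and 12 months post-surgery").

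The Discussion names two kinds of risk. The first is general surgical risk: anaesthesia, superficial or deep infection, and slow wound healing. The second concerns pain: "there is a risk that the treatment results in no relief or a worse pain situation for the participant".

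Other safety handling is under Data collection and management. Site investigators record adverse events at each visit and report them to the principal investigator and trial coordinator within three working days. A project-independent GCP monitor monitors the study twice a year.

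**The concern.** Each participant receives the study treatment once, as an operation. A review of accumulating harms can change little about that exposure for people already operated on; it chiefly protects those still waiting. A trigger that needs a full year of follow-up, in a trial meant to recruit in two to three years, puts the look near or after the end of recruitment.

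The surgical risks in the Discussion belong by their nature to the period around and soon after the operation, and adverse events are already collected at the 1- and 3-month visits. For those risks, waiting until month 12 delays the look without adding much to it. A difference between arms is also conceivable, because RPNI adds a muscle donor site that the other two procedures lack. At stake is how much protection the review gives. The primary estimate and its type I error are not affected.

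**Working it through.** **The plan's own figure.** Sample size needs 33 per group, 99 in total, for the 1:1 comparisons and expects about 10% drop-out. 99 / 0.90 = 110, which agrees with the article. Half of the study population is read as 55.

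**Inputs.** N = 110 (Sample size). Trigger: 55 participants past 12 months (Statistical analyses). Recruitment length D = 24 to 36 months, from early 2023 to early or late 2025 (Trial status). The accrual pattern is not stated; uniform accrual is assumed first, with surgery at randomisation.

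**Formula.** The 55th participant enters at D/2 and passes a visit at m months at D/2 + m. The share randomised by then is min(1, (D/2 + m)/D).

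| D (months) | 1-year trigger (m = 12) | Not yet randomised | 3-month trigger (m = 3) | 1-month trigger (m = 1) |
|---|---|---|---|---|
| 24 | 24/24 = 100%, 110 | 0 | 15/24, about 69 | 13/24, about 60 |
| 30 | 27/30 = 90%, 99 | 11 | 18/30, 66 | 16/30, about 59 |
| 36 | 30/36 = 83%, about 92 | about 18 | 21/36, about 64 | 19/36, about 58 |

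An early trigger would therefore leave about 41 (110 − 69) to 52 (110 − 58) people still to be randomised, against 0 to 18 under the present rule.

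**Sensitivity at D = 36, 1-year trigger.**

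- *Lag from randomisation to surgery.* 1 month: 31/36 = 86%. 3 months: 33/36 = 92%.
- *55 actual completers required, with 10% drop-out.* 55/0.9 = 61.1 must have entered, so 61.1/110 + 12/36 = 89%.
- *Ramp-up, cumulative share (t/D)^a.* a = 1.5 gives 94%; a = 2 gives 100%.
- *Front-loaded, same form.* With a = 0.5 the 55th enters at 36 × 0.25 = 9 months and the share is (21/36)^0.5 = 76%. With a = 0.7 it is 78%.

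**Outside the stated window.** If recruitment slips to 4 or 5 years, the uniform share is 1/2 + 1/4 = 75% or 1/2 + 1/5 = 70%, leaving about 27 to 33 people.

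Within the stated window, every pattern tried has at least about three quarters of participants randomised before the review.

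**The case against.** A reader might infer that the trial has no other independent safety review. The documents do not support that. This is a journal article condensing a longer protocol, and committee schedules are commonly left to that document or a charter. What can be said is that this is the only such review the article describes.

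A reader might also infer that nobody is left to protect, or that the 1-year look serves no purpose. Neither follows. At 30 and 36 months of uniform recruitment, 11 and about 18 people remain unrandomised; only the 24-month case leaves none. The Discussion also names worsening pain as a risk, which an early look cannot assess at 12 months. Trial design lets dissatisfied participants request another of the procedures after month 12, and 1-year data can inform those decisions. The 1-year trigger therefore has a rationale.

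Other safeguards exist: rapid adverse event reporting, the GCP monitor, and the site investigator's power to end an individual's participation for safety. Site investigators also know the allocation. These matter, but none is described as an independent review of accumulated harms by arm. Reports go to the trial's own team. Data Availability withholds the document linking treatment to participant code until after the 1-year analyses. At the stated 9 hospitals, a site averages 110/9, about 12 participants or 4 per arm, too few to show a difference in harms.

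Finally, all three procedures are already described in the literature, so the intensity of monitoring is partly judgement. That is a reason to ask for a modest addition and not to treat the point as a defect in validity. The accrual objection cuts both ways: front-loading or slippage lowers the share, while ramp-up or a lag to surgery raises it.

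**Conclusion.** The point stands in limited form. The stated trigger and recruitment window together place the described safety review when about 83–100% of participants (92 to 110 of 110) have been randomised. This rests on uniform accrual over 24 to 36 months and on reading half as 55; front-loading brings the 36-month figure to about 76–78%. For the surgical risks the article names, that is too late to protect most participants. The review keeps some value for the 0 to 18 not yet randomised, for worsening pain, and for procedures after month 12. The trial's estimates and error rates are untouched; it is an improvement worth making to a safeguard the plan already provides.

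**What to change.** Keep the 1-year review. Add an earlier review by the same committee when half the participants have completed the 1-month or 3-month visit, which under uniform recruitment falls at about 58–60 or 64–69 randomised respectively. Restrict it to adverse event data, with no test of the primary outcome, so that no alpha is spent. If the full protocol or the committee's charter already provides earlier or repeated reviews, say so in the article instead.

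The cost is a sentence in the protocol or charter and one extra meeting of a committee that is already planned. The visits and adverse event records it needs are already collected.

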## Discussion

Investigation in pain-related studies is challenging due to an absence of objective evaluation methods. Pain is a subjective experience that is difficult to quantify independently among participants. In our study design, we have tried to mitigate this problem by using different protocols and questionnaires for pain tracking that have previously been used in clinical settings.

One of the main challenges in this RCT is to recruit a sufficient number of potential candidates meeting our inclusion criteria within an acceptable time. For example, it took over 3 years for Dumanian et al. (2019) to gather 28 participants who met their study criteria [12], and this study was performed in the USA (with a larger amputee population compared to Sweden, Italy, Canada, Chile, and the UK). According to Sweden’s amputation and prothesis registry for lower extremities (SwedeAmp) yearly report in 2019, the mean age of amputation for women is 78 and for men is 72 years old. Furthermore, 61% of all amputated women and 58% of all amputated men are in the range of 70–89 years old, and 84% of all Swedish amputees have either diabetes and/or vascular disease. We expect this to add a significant challenge in the volume of participants required. Our recruitment approach therefore includes close contact with prosthetic centres, orthopaedics, and hand surgeons in the participating hospitals.

The surgical treatment approach requires that the participants undergo surgery; thus, general surgical risk applies, including but not limited to those associated with anaesthesia, the possibility of superficial or deep bacterial infections, and delayed wound healing. Even though the surgical approaches have shown potential for postamputation pain reduction [12, 13], there is a risk that the treatment results in no relief or a worse pain situation for the participant. This may lead to a need for increased pain suppression medication.

This RCT is designed as a double-blind study, where both the participants and the evaluator are unaware of which surgical treatment has been prescribed. However, since RPNI involves a muscle graft from a donor site, the RPNI participants will have an additional scar compared to TMR and the neuroma transposition group. We discounted the option to add a sham scar to participants from the other groups on ethical grounds and instead designed the RCT such that participants will not be told detailed methodological differences between the surgeries, and we do not expect them to know which surgical treatment they received. The participants can find out which treatment they received by searching in the literature, but even in that unlikely case, they still would not know which one of the surgeries is the reconstructive one or the active control.

## Trial status

This clinical study was registered at ClinicalTrials.gov on 17 August 2021 with registration number NCT05009394. This is protocol version 4 (2022–12-21). Recruitment of participants is expected to take place in early 2023 and is expected to be completed in 2025.

## Data Availability

The clinical investigators and the principal investigator have full access to all study-specific data, except for the document including the link between surgical treatment and participant’s code number. That document will only be accessible after the 1-year follow-up analyses. They have the responsibility for correct data storing and for the accuracy of the data analysis.

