## Methods/design

### Participants

#### Recruitment and inclusion of participants

Potential participants will be identified and recruited by healthcare professionals or among people who have had earlier contact with the research groups. Clinical trial brochures will be distributed to prosthetic clinics and orthopaedic and hand surgery departments. The trial will be advertised on social media, in local newspapers, and at national conferences in Sweden, Italy, Canada, Chile, Australia, UK, and USA. Persons interested in participating will be provided with written information about the study, and they will be directed to a pre-screening form either in paper or digital format (Additional file 1). After submission of the pre-screening form, the potential participant will be contacted by phone or via email. If the potential participant is interested in participating in the study, the participant will be provided with an informed consent form (ICF) (Additional file 2) and invited to a screening visit. At the screening visit, the clinical investigator on site will perform a physical examination, and the participants answer any questions. Answers to the pre-screening form will be used in combination with the screening visit to determine eligibility for the study. The informed consent form will be signed by the participant and the site clinical investigator before collecting any study-specific data. The following are the study eligibility criteria.

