The following are the inclusion criteria:The participant must have a major limb amputation.The participant is ≥ 18 years old at the time of consent.The participant must be in generally good health to undergo a surgical intervention, as per the clinical investigator’s opinion.Time since the last amputation must be over a year at the time of consent.The participant must have an average residual limb pain score equal or greater than 4 on the Numerical Rating Scale (NRS, 0–10) after the baseline period.If the participant has been prescribed pharmacological treatments for pain, there must be no variations in dosage (steady consumption) for at least 1 month before the screening visit.If the participant has been prescribed non-pharmacological treatments for pain, such as spinal cord stimulation, transcutaneous electrical nerve stimulation, and mirror therapy, the treatment must have ended at least 1 month before the screening visit.The participant must have a stable prosthetic fitting for at least a month before the screening visit.The participant has a sufficient understanding of the language in which the assessments will be conducted, as per the clinical investigator’s opinion.

The following are the exclusion criteria:Neurological or other conditions that affect nerve regeneration for the nerve to be treated.Active infection in the residual limb.Prior RPNI or TMR surgery of the nerve to be treated (with painful neuroma) to address postamputation pain.Mental disorders (e.g., schizophrenia, paranoia, psychosis, etc.), reluctance, or language difficulties that result in difficulty understanding the meaning of study participation.Ongoing participation in a clinical study that the clinical investigator deems detrimental to participation in this study.

During this clinical trial, participants will not be forbidden to receive other pain treatments if deemed necessary by their physician. All pain treatments received during the clinical trial will be recorded.

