#### Withdrawal or termination of individual participants

Participants can discontinue their participation in the study at any time, without any consequences on their clinical treatment at their respective hospitals or health care systems. The clinical investigator at the site can at any time terminate participation in the study for an individual if the participant’s safety can no longer be maintained due to any harmful clinical event, clinical anomalies, if other medical conditions or situations occur, or if the participant no longer fulfils the study criteria due to recently developed or not previously recognised disorders. Adverse events (AE) will be presented together with the results of the study.

We will employ the intention-to-treat (ITT) methodology in the analysis of the primary outcome. In case of non-adherence to the protocol, such as crossovers between surgical interventions after randomisation, the data will be analysed by grouping participants to their originally allocated intervention. Furthermore, the last collected data point will be used in the primary analysis in the case that data is missing due withdrawal, termination, or missed follow-ups. A sensitivity analysis of the primary analysis will be performed. A complementary analysis of the primary outcome will also be performed on the per-protocol (PP) population. The secondary outcomes will be analyses on both ITT and PP populations. Based on previous studies, drop-outs are expected to be around 10%.

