### Blinding

The study is designed so that the participant and the evaluator are blinded to the surgical treatment the participant has received. The participants will undergo the same study-specific assessments despite their assigned surgical treatment. The only difference between the groups will be the surgical treatment, although the participants in the RPNI group will have an additional scar on the muscle donor site (inconceivable to the participant) compared to the TMR and neuroma transposition group. The participants will not have any expectation of surgical outcome superiority since the trial will be communicated as a comparison between three surgical treatments formerly described in the literature. The evaluator and the participant will be unaware of which surgical treatment the participant has received up to 12 months post-surgery. Thereafter, the study will be unblinded for the participants and the evaluator. The clinical investigator in each site will be aware of the treatment allocation, and they are excluded from the analyses. The raw data following the outcome assessments from each surgical treatment will have the same structure, which make it unfeasible to differentiate the group assignments without having the document that links the specific treatments to participants’ code numbers.

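### At their own site, withholding the link document does not stop clinical investigators, who already know the allocation, from reading accumulating pain scores by operation while recruitment is open

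*Protocol article*

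**What the plan says.** Four parts of the protocol article bear on this.

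- **Data Availability** gives access: "The clinical investigators and the principal investigator have full access to all study-specific data, except for the document including the link between surgical treatment" and the participant's code. On that document it adds: "That document will only be accessible after the 1-year follow-up analyses".
- **Blinding** relies on the same document. The outcome data from all arms share one structure, "which make it unfeasible to differentiate the group assignments without having the document that links the specific treatments" to the codes. The same paragraph says: "The clinical investigator in each site will be aware of the treatment allocation, and they are excluded from the analyses". Only the participant and the evaluator are blinded, up to 12 months.
- **Data collection and management** has the evaluator document outcomes in case report forms that carry participant codes. It has the clinical investigator discuss adverse events with the participant at each visit and enter them in that participant's form. Data access is limited to researchers directly involved, with no narrower rule by role.
- **Recruitment and inclusion** and **Withdrawal or termination** set out what the investigator decides. "At the screening visit, the clinical investigator on site will perform a physical examination". The criterion "The participant must be in generally good health to undergo a surgical intervention" is judged on the investigator's opinion, as is language understanding. Later, "The clinical investigator at the site can at any time terminate participation in the study for an individual", on grounds that the section then lists.

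Trial status expects recruitment from early 2023, to be completed in 2025.

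**The concern.** The only stated barrier between investigators and results by arm is the link document. For their own patients they do not need it: they know who had which operation, and they work in the coded form. The barrier therefore fails for the people most able to act on what they see.

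Three things are at stake. An impression that one operation does better locally could colour opinion-based eligibility judgements. It could colour what participants, who are meant to be blinded, hear at visits where adverse events are discussed, and the primary outcome is a self-reported score. It could also colour a decision to end participation. That last route touches the primary analysis directly, because both the withdrawal section and Statistical analyses replace a missing 12-month value with the last one collected. Someone who knows the arm and the current score would be deciding when the analysed value becomes fixed.

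The plan elsewhere gives the mid-trial examination of data to an independent committee, and for safety only. Open access to follow-up scores for unblinded site staff sits badly with that.

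**Working it through.** **Reading the sections together**

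1. Who knows the arm? The site's clinical investigator (Blinding).
2. Can a code be matched to a patient? Yes, locally: the investigator enters adverse events in that patient's coded form (Data collection and management).
3. Can that person see pain scores? Yes: full access to all study data apart from the link document (Data Availability).
4. When? The text does not say outright that access runs during the trial. But an exception that lifts only after the 1-year analyses makes sense only if the other access comes earlier.
5. Is recruitment open then? Yes. With enrolment from early 2023 into 2025, the 1-, 3-, 6- and 12-month scores of early participants arrive while later ones are being screened.
6. How far does it reach? Only to the investigator's own site. Other sites' arms remain masked by the withheld document, roughly eight-ninths of the data if the 9 hospitals recruit equally.

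**The plan's own figures**

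Inputs from Sample size: SD 2.2 (TMR, RPNI) and 3.3 (control), difference 2.0, 5% level (two-sided per Statistical analyses), power 80%.

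- Normal approximation, 1:1: n per group = (1.960 + 0.842)² × (2.2² + 3.3²) / 2² = 30.9, so 31. Unequal-variance t power is 0.812 at the stated 33 per group.
- Drop-out: 99 / 0.9 = 110.

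The stated sizes reproduce and are not in question. They supply the SDs and the total used next.

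**How noisy a local comparison would be**

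Assumption: equal recruitment and complete outcomes. Then 110 / 9 ≈ 12 per hospital, or 8 reconstructed and 4 control. With no true difference, P(|difference| ≥ 2) = 2 × [1 − Φ(2 / SE)].

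| SD assumed (reconstructed, control) | SE | P |
|---|---|---|
| 2.2, 2.2 | √(2.2²/8 + 2.2²/4) = 1.35 | 0.14 |
| 2.2, 3.3 (the plan's) | √(2.2²/8 + 3.3²/4) = 1.82 | 0.27 |
| 3.3, 3.3 | √(3.3²/8 + 3.3²/4) = 2.02 | 0.32 |

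About 14–32% of sites would thus see, by chance alone, a gap as large as the difference the trial is designed to detect. During recruitment fewer than 12 participants per site would have follow-up scores, which raises all three probabilities.

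**How much one termination could move the result**

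The document gives no rate of investigator-led termination; the 10% drop-out covers all causes (0.10 × 110 = 11 participants). As an illustration, suppose one control participant's carried-forward score differs by 2 points from the unseen 12-month score. That moves the control mean by 2 / 37 = 0.05 points. Several such cases in one direction would be needed to matter.

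**The case against.** The strongest case on the other side has five parts.

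- **Timing and detail.** Data Availability is a short statement in a condensed article, and user rights by role are commonly left to the full protocol or data management plan. That would answer a complaint about missing detail. It does not answer a sentence that positively grants full access, and the timing of the exception supports reading that access as falling within the trial.
- **The operating team cannot be blinded.** This stands, and investigators will form impressions from ordinary contact with patients. But knowing the operation is unavoidable; having every local participant's scores to set beside it is not.
- **Eligibility precedes allocation.** This largely stands. REDCap minimisation allocates only after the criteria are met, so a shift in who is enrolled changes the case mix of all arms together. A reader might infer selection between arms; the documents do not support that.
- **Termination is limited.** This also stands in part. The quoted power is followed by listed grounds: safety, medical conditions or situations, and no longer meeting the criteria. Pain scores are not among them, so a reader should not infer that investigators may remove participants at will. Judgement within those grounds remains, and the carried-forward value makes it count.
- **Outcome assessment is protected.** Participant and evaluator are blinded to 12 months, and the evaluator documents outcomes.

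Two further inferences go too far. One is that withholding the link document achieves nothing; it still masks the other sites. The other is that the chance-difference figure measures harm. It shows only that small local comparisons mislead easily, and says nothing about how often anyone would act on them.

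A neighbouring conflict should be reconciled too: Blinding excludes clinical investigators from the analyses, while Data Availability says of them and the principal investigator, "They have the responsibility for correct data storing and for the accuracy of the data analysis". The present point does not depend on it.

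**Conclusion.** The concern holds for each investigator's own site. The stated safeguard does not prevent an unblinded clinical investigator from following local 1- to 12-month pain scores by operation while recruitment is open, and that person retains judgement over eligibility and, on listed grounds, over continued participation.

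The documents do not establish trial-wide access to results by arm, nor that bias has occurred. Blinded participants and evaluators and software allocation limit the routes. The effect on the primary estimate cannot be quantified from the document. The 14–32% range is an indication of local noise, resting on equal recruitment, complete outcomes and normally distributed differences. The sample size is unaffected. Because the change is specific and cheap, it is worth making even though the risk is moderate.

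**What to change.** Amend Data Availability, and align Blinding with it, along these lines:

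> Until the data for the 1-year analysis are locked, clinical investigators have access only to eligibility data (including baseline scores), operative data and adverse-event data for their own site. Post-surgery pain surveys and questionnaires are accessible only to the blinded evaluator and the data manager. After a participant's 12-month visit and unblinding, that participant's own scores may be released to the clinical investigator for the outcome consultation.

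The last sentence is needed because Trial design and the Fig. 2 legend have treatment outcomes discussed with the clinical investigator after the 12-month unblinding. Early participants will reach that point well before the lock. Adverse-event reporting is unchanged.

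The cost is a change of user rights by form if the case report forms are held in REDCap, or separate adverse-event and pain forms if they are on paper, plus these few sentences. The downside is that investigators can no longer browse follow-up scores and must ask about pain in ordinary care. If the chance-difference figure is cited in support, give it as the range above with its assumptions.
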